### Participants

Participants will be recruited from the following universities: Kagoshima University, University of Fukui, Shigakukan University, Naruto University of Education, Jin‐ai University, Hiroshima Cosmopolitan University, Teikyo University, Shujitsu University, Tottori University, Fukushima Gakuin University, Tokyo Rissho Junior College, and Senshu University. Additionally, participant enrollment will be solicited through the research project website. The predetermined inclusion and exclusion criteria outline the specific requirements that potential participants must meet for enrollment in the trial.

Inclusion criteria:
1.A total score of 10 or higher on a measure of gaze anxiety symptoms using the Gaze Anxiety Rating Scale (GARS).^3^
2.Enrollment as a university and graduate student aged between 18 and 30 years.3.Capacity to send and receive electronic mail.4.No planned transfer or withdrawal from their academic institution during the study period.

Exclusion criteria:
1.Presence of mental disorders, including but not limited to major depressive disorder and SAD.2.A history of suicidal ideation or attempts.3.Presence of a progressive medical illness (e.g., cancer).4.Pregnancy or the immediate postpartum period.5.Any condition or behavior deemed by the researchers to render the individual unsuitable for participation in this study (e.g., antisocial behavior).

For participants identified as being at risk for mental health conditions, the researchers from each university will inform the principal investigator ([name]), who has been the study secretariat, to assess their eligibility by using the Mini‐International Neuropsychiatric Interview (MINI).^13^, ^14^

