### Outcome

All outcome measures will be structured as web‐based questionnaires and sent to the participants' email addresses at baseline, post‐intervention (5 weeks follow‐up), 3 months follow‐up, and 6 months follow‐up. To promote participant retention and follow‐up completion, monthly email reminders will be sent from the start of the intervention until the end of the follow‐up period. Any deviations from the trial intervention will be recorded during follow‐up assessments.

The primary outcome will be the GARS used to measure the severity of clinical symptoms and rate anxiety/fear and avoidance of gaze. The GARS comprises 17 items regarding social situations involving focused gaze.^3^ For each item, participants will rate the degree of anxiety/fear and the frequency of avoidance on a scale from 0 (“no anxiety” or “no avoidance”) to 3 (“a lot of anxiety” or “avoid a lot”). The total GARS score ranges from 0 to 102, with higher scores indicating a greater severity of gaze anxiety. The validity and reliability of the GARS have been demonstrated in the original English and German versions.^3^, ^17^, ^18^ The Japanese version of the Gaze Anxiety Rating Scale (GARS‐j) was developed through translation into Japanese by the first author ([name]) and back‐translation by the second author ([name]), with the resulting text being reviewed by the original scale developers (please refer to the GARS‐j in the Supporting Information).^19^ Furthermore, the validity of the GARS‐j will be examined using baseline responses from this trial. Table 3 shows secondary outcomes.

**Table 3 pcn570236-tbl-0003:** Secondary outcomes.

Outcome	Description
LSAS‐j	The LSAS‐j includes 24 social situations related to “fear or anxiety” and “avoidance,” which participants rank on a 4‐point scale (0 = never, 4 = severe), has a total score range of 0–144.^20^ The Japanese version of the LSAS has demonstrated reliability and validity and is widely used in Japanese clinical and research settings.^21^ Therapeutic response will be defined as a ≥28% decrease in the LSAS total score.^22^ Remission will be defined as an LSAS total score of <35,^23^ consistent with a previous RCT.^10^ Conversely, worsening will be defined as a ≥28% increase in LSAS total score to assess the risk of exacerbating social anxiety.

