SPIN	The SPIN is a self‐rating scale that measures 3 characteristic aspects of SAD: fear, avoidance, and physiological arousal.^24^ In the Japanese version of the SPIN, 17 questions are answered on a 5‐point scale, with 0 = not at all applicable and 4 = extremely applicable.^25^
PHQ‐9	Depressive symptoms will be assessed using the Japanese version of the PHQ‐9.^26^ The initial nine items of the PHQ‐9 inquire about the frequency with which symptoms of major depressive disorder have occurred over the past 2 weeks. For each item, participants select a response from 0 (not at all) to 3 (nearly every day), yielding a total score ranging from 0 to 27, with higher scores indicating a greater severity of depressive symptoms.^27^
GAD‐7	Generalized anxiety will be assessed using the Japanese version of the GAD‐7.^26^ The initial seven items of the GAD‐7 inquire about the frequency with which symptoms of generalized anxiety disorder have occurred over the past 2 weeks. For each item, participants select a response from 0 (not at all) to 3 (nearly every day), yielding a total score ranging from 0 to 21, with higher scores indicating a greater severity of generalized anxiety symptoms.^28^

*Note*: We will also calculate recovery rates based on the Improved Access to Psychological Therapies program criteria and improvement (recovery) rates defined as achieving total scores of SPIN < 19 and PHQ‐9 < 10 simultaneously.^29^ This definition has been used as a benchmark for improvement from SAD.

Abbreviations: GAD‐7, Generalized Anxiety Disorder‐7; LSAS‐j, Japanese version of the Liebowitz Social Anxiety Scale; PHQ‐9, Patient Health Questionnaire‐9; SAD, social anxiety disorder; SPIN, Social Phobia Inventory.

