### Adverse events

We will instruct all participants at each university to immediately report any adverse events that occur during this trial period. If additional support is needed, participants will be referred to campus counseling services or encouraged to visit local clinics affiliated with their universities. Even if no adverse events are reported, participants scoring 10 or above on the Patient Health Questionnaire‐9 (PHQ‐9) total score during the follow‐up period will assess their mental health problem by using the MINI.^13^, ^26^ Based on the results of this assessment, participants may be recommended to see a medical doctor.

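### The only score-based safety trigger in follow-up reads the PHQ-9 total (10 or above), so a non-zero self-harm answer with a total of 9 or less does not lead to a MINI

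*Protocol article*

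**What the plan says.** The Adverse events section of the protocol article gives two routes to help during the trial.

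- **Reporting.** Participants are told to report adverse events at once, and "If additional support is needed, participants will be referred to campus counseling services" or encouraged to visit a local clinic.
- **Score rule.** This is introduced with the words "Even if no adverse events are reported" and applies to "participants scoring 10 or above on the Patient Health Questionnaire‐9 (PHQ‐9) total score during the follow‐up period". These participants are assessed with the MINI and, depending on the result, may be advised to see a doctor.

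The Outcome section describes how the scores arise: "All outcome measures will be structured as web‐based questionnaires", sent by email at baseline and at three later points. Table 3 describes the PHQ-9 as nine items on depressive symptoms, each answered 0 to 3, "yielding a total score ranging from 0 to 27".

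The Participants section lists "A history of suicidal ideation or attempts" as an exclusion criterion. For people identified as at risk, it says "the researchers from each university will inform the principal investigator", and the stated purpose is "to assess their eligibility by using the" MINI. That notice is therefore written for entry, not for follow-up.

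**The concern.** The score rule exists to catch participants who have not come forward. It is the one published follow-up route that does not depend on the participant volunteering a problem. A sum score suits a question about overall depressive burden. It suits a single answer on self-harm poorly, because eight low answers can hide one serious one.

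The sponsor treats past suicidal ideation as serious enough to exclude on, yet publishes no follow-up rule aimed at ideation that emerges after entry. The setting adds weight. Both interventions are self-help without a therapist running sessions, both include work on social trauma, and the control arm receives no active intervention during the study. With outcomes collected online, the questionnaire answer may be the only signal the team receives. If the rule is applied as written, a participant could tell the trial about thoughts of death or self-harm and not be assessed.

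**Working it through.** **Inputs**

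- Trigger: PHQ-9 total of 10 or more (Adverse events).
- Scale: nine items, each 0 to 3 (Outcome, Table 3).
- Follow-up questionnaires: three, at Weeks 5, 13 and 26 (Outcome; Statistical analysis plan).
- Planned sample: 249, with 20% attrition (Sample size).
- Assumption: one of the nine items asks about thoughts of death or self-harm. The article prints no item text, so the sponsor should check its own form.

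**Reproducing the stated range.** 9 × 3 = 27, which matches Table 3. An eight-item form would give 8 × 3 = 24, so all nine items enter the total.

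**What the rule misses.** The highest total that does not trigger it is 9. With a self-harm answer of *a*, the participant is missed when the other eight items sum to 9 − *a* or less, and reached from 10 − *a*.

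| Self-harm answer | Missed if other eight sum to | Totals missed | Reached if other eight sum to | Mean per other item needed |
|---|---|---|---|---|
| 1 | 9 − 1 = 8 or less | 1 to 9 | 9 or more | 9/8 = 1.125 |
| 2 | 9 − 2 = 7 or less | 2 to 9 | 8 or more | 8/8 = 1.0 |
| 3 | 9 − 3 = 6 or less | 3 to 9 | 7 or more | 7/8 = 0.875 |

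The same gap recurs at each of the three follow-up questionnaires.

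**Whether another published route closes it**

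- Adverse-event reports (Adverse events) and the offer to contact researchers at any time (Ethics and dissemination) both need the participant to act.
- The report of unintended treatments or care (Adherence) is also self-reported, and asks about care received rather than symptoms.
- Referral for additional support (Adverse events) works once a need is known; no score or answer is given that would reveal it.
- LSAS worsening, an increase of 28% or more (Table 3), is an analysed outcome with no clinical action attached.
- The exclusions and the MINI under Participants operate at entry.

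None of these turns a follow-up questionnaire answer into an assessment.

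**Checking load if the rule is widened.** At full return, 249 × 3 = 747 questionnaires. If all the attrition falls before Week 5 (an assumption about timing), 249 × 0.8 = 199.2, so about 199 × 3 = 597.

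**The case against.** There are four serious objections.

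1. **The self-harm item is not in the article.** This is true, and the point falls away if the sponsor's form has no such item. But the article names the instrument, describes its items as symptoms of major depressive disorder, and gives a range that only nine items can produce. The assumption is declared and can be settled by looking at the form.

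2. **A condensed article leaves operational safety detail to the full protocol.** An item-level rule may exist there, and nothing in the article says the total is the only ground for a MINI. That possibility stands and limits the claim to the rule as published. However, the article does not leave the matter open: it states a specific trigger, score and action, and a reader would take these as the operating rule. The criticism is of how that rule is set.

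3. **Other safeguards exist, and the population is non-clinical.** Both are true. The entry exclusions lower the risk, though by how much cannot be judged from the article, and the voluntary routes remain open. They leave the gap in place for a participant who answers the item but reports nothing.

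4. **No frequency can be given, and a full MINI for every non-zero answer is only one possible response.** Both points stand. The table shows which answers are missed, not how often they occur. A brief check first would be a reasonable alternative. What matters is that the answer itself leads to a review.

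**Conclusion.** The concern holds as a coverage gap in a stated rule. It does not contradict the exclusion criteria, and it does not mean the trial lacks safety measures. As published, the score rule misses a self-harm answer of 1, 2 or 3 at totals of 1 to 9, 2 to 9 and 3 to 9 respectively, at each of three assessments.

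This rests on the sponsor's PHQ-9 carrying the standard self-harm item, and on no item-level rule existing in the full protocol, which was not available. The number of participants affected is unknown and no estimate is offered. The consequence for an individual could be serious and the remedy is cheap, so the sponsor should make the change. Confidence is medium because of the two conditions above.

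**What to change.** - In Adverse events, make the trigger a PHQ-9 total of 10 or above **or** any non-zero answer on the self-harm item at a follow-up assessment, leading to prompt review and the MINI.
- In Participants, extend the notice to the principal investigator, who acts as study secretariat, so that it also covers follow-up.
- If the full protocol already has an item-level rule, state it in Adverse events.

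The text change is one clause in each section, and the answers are already collected. The real cost is operational. Someone, or an automated alert (none is described), must check the item as each questionnaire comes in. That is between about 597 and 747 returns on the attrition assumptions shown above. There would also be some extra MINI assessments, whose number the article does not allow to be estimated.

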### Adherence

We will assess adherence to the two interventions using two methods. In the book group, participants will be asked to report the chapters of the self‐help book read and cognitive‐behavioral techniques practiced in daily life at the initial outcome assessment. For the web‐based CBT intervention, the e‐learning system will record completed treatment modules automatically, and participants will also report cognitive‐behavioral techniques practiced in daily life at the initial outcome assessment. All participants, including the control group, will be asked to report any unintended treatments or care received during the study period.

### Statistical analysis plan

Statistical analyses will be performed by the second author ([name]) using IBM spss Statistics (IBM Corp., Armonk, NY, USA) and will adhere to the intention‐to‐treat principle. The analyst was not involved in creating the two intervention programs. The analyst will be concealed to group allocation when accessing the data. This means she will not know which specific intervention a group received or if each participant was in the control condition.

Descriptive statistics will be used to summarize demographic data (including participants' age and sex) and the severity of clinical symptoms on each scale. Group differences will be compared to determine statistical significance. As a primary analysis, mixed‐effects models will examine significant differences in the mean change in total scores on each symptom rating scale between the groups from baseline to Week 5 (1 month), Week 13 (3 months), and Week 26 (6 months) post‐intervention. If an overall significant difference is found, multiple comparisons will be conducted. For multiple comparisons, we will implement Dunnett's test to control for inflated Type I error rates.^33^ Effect sizes will be calculated between and within the groups. The significance level for hypothesis testing will be set at a two‐tailed *α* of 0.05, and 95% two‐sided confidence intervals will be calculated.

For the binary variables of treatment response, remission, and worsening, the odds and risk ratios between the groups will be analyzed using Fisher's exact test. To further evaluate the risk of worsening social anxiety, as measured by the LSAS, we will calculate the risk ratio, relative risk reduction, absolute risk reduction, and number needed to treat.

We plan to conduct a sensitivity analysis excluding participants with insufficient engagement in the self‐help intervention and those who provided implausible response patterns—specifically, patterns like straight‐lining, contradictory responses, or inconsistent responses between the GARS‐j and the LSAS‐j. Participants will be defined as having sufficient engagement if those in the self‐help book group have completed at least two chapters, and those in the ICBT group have reached the “Behavioral Experiments” treatment module. The sensitivity analysis, similar to the primary analysis, will be performed after imputing missing values using R's “mice” package.^34^

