### Sample size

The sample size for this study was set at 249 (Figure 1), considering the following G*Power estimated values and a 20% attrition rate (version 3.1.9.7; The G*Power Team).^30^, ^31^ We set the parameters for the *F* tests—anova: fixed effects, omnibus, one‐way, with an effect size *F* = 0.25 (medium), an *α* error probability of 0.05, and a power (1 − *β* error probability) of 0.9 for three groups. These inputs yielded a noncentrality parameter of 12.94, a critical *F* of 3.04, an original total sample size of 207, and an actual power of 0.902.

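### The primary analysis of GARS names no time point among Weeks 5, 13 and 26, and Dunnett's test does not adjust across them, so the stated 5% error rate is not strongly controlled

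*Protocol article*

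**What the plan says.** The Outcome section is clear about the endpoint: "The primary outcome will be the GARS used to measure the severity of clinical symptoms". Table 3 lists LSAS-j, SPIN, PHQ-9 and GAD-7 as secondary.

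The Statistical analysis plan section describes the primary analysis as mixed-effects comparisons of "mean change in total scores on each symptom rating scale between the groups from baseline to Week 5 (1 month), Week 13 (3 months"; its list of assessments ends at Week 26. It then says: "If an overall significant difference is found, multiple comparisons will be conducted". Dunnett's test is the method for those comparisons and is presented as the control on type I error. "The significance level for hypothesis testing will be set at a two‐tailed *α* of 0.05" applies throughout. The section does not say which time point is primary, whether the overall test is one joint test or one per time point, or whether anything adjusts across times.

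The Abstract ties the primary outcome to baseline, 3 months and 6 months, without Week 5. The Sample size section powers a single one-way omnibus F test, "with an effect size *F* = 0.25 (medium"), and names no occasion for it.

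**The concern.** With two active arms and three times there are 2 × 3 = 6 GARS contrasts against control. Dunnett's test handles the two that share a control at one time and does nothing across the three times. A preceding overall test protects fully only when there is no effect anywhere. Once a real effect opens it, the remaining null contrasts are tested without that protection.

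The times are not interchangeable. The book schedule runs 5 weeks (Table 1) and the ICBT schedule 10 weeks at one module per week (Table 2). Week 5 is therefore the end of one intervention and the midpoint of the other. Without a designated time, a claim that an arm is effective could rest on whichever assessment favours it. Outcomes are self-rated in an unblinded trial against no treatment, which makes a fixed primary contrast more valuable.

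The wording that puts every scale under the primary analysis also contradicts the Outcome section.

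**Working it through.** **Inputs from the article.** Two-sided α 0.05; three arms, 1:1:1; f = 0.25; 207 evaluable participants, so 207/3 = 69 per arm; GARS at Weeks 5, 13 and 26; overall test, then Dunnett.

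**Assumed, because the article gives no value.** Correlation between time points of 0.3 to 0.8; a standardised effect of 0.6 where an effect is placed.

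**The plan's own figure.** Noncentrality = N f² = 207 × 0.0625 = 12.94; critical F(2, 204) = 3.04; power 0.902. This reproduces the stated "an original total sample size of 207, and an actual power of 0.902".

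**Dunnett at one time.** With 2 contrasts, correlation 0.5 between them (equal arms) and 204 degrees of freedom, the two-sided critical value is 2.2275, or 0.0270 per contrast. Simulated familywise error at one time is 5.0 to 5.1%, as it should be.

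**Three times.** If the times were independent and there were no overall test, the error would be 1 − 0.95³ = 14.3%. With correlated times (simulation, 200,000 runs, 69 per arm), the chance of at least one false Dunnett rejection on GARS, in %, is:

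| Between-time correlation | Nothing works: overall test at each time | Nothing works: one joint overall test | Both arms work at Week 5 only; false finding at Week 13 or 26: test at each time | Same: one joint test |
|---|---|---|---|---|
| 0.3 | 10.3 | 3.9 | 7.0 | 9.3 |
| 0.5 | 9.5 | 3.5 | 6.9 | 9.2 |
| 0.7 | 8.5 | 3.0 | 6.4 | 8.5 |
| 0.8 | 7.6 | 2.8 | 5.9 | 7.9 |

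If instead one arm works at all three times and the other never does, the null arm is falsely declared at some time in 5.5 to 7.6% under either form of overall test. A repeat with a different implementation gave values up to about 0.7 points lower (for example 7.2 to 9.7% in the first results column), so the conclusions are quoted to about a whole point.

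Each form of the overall test exceeds 5% somewhere. A test at each time fails already when nothing works. A joint test holds when nothing works and fails once something does.

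**Power if one time point is fixed.** For means (0, 0, d) or (0, d, d), the SD of the three means is d√2/3, so f = 0.25 gives d = 0.25 × 3/√2 = 0.53. At 69 per arm:

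| True pattern | Dunnett alone | After an overall F test |
|---|---|---|
| One effective arm, d = 0.53: that arm | 81.2% | 80.2% |
| Both arms, d = 0.53: at least one | 92.0% | 90.1% |
| Both arms, d = 0.53: both | 70.5% | 70.5% |
| Graded effects (0, 0.31, 0.61): at least one | 92.0% | 89.8% |

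At a single time point, Dunnett needs no preceding test; the overall test costs 0 to about 2 points.

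**The case against.** The strongest reply is that a single joint overall test is a natural reading of the plan, and under it the error when nothing works is 2.8 to 3.9%, below 5%. That stands for the global null. It does not extend to configurations in which one arm or one time shows a real effect, and those are the ones that matter when specific claims are made.

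A second reply is that a journal article leaves detail to the full plan. That would excuse silence about the model's form. Here, however, the article itself defines the primary analysis over three times and names Dunnett as the control on type I error. Its wording on scales also conflicts with its own Outcome section, and another document would not remove that conflict.

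Three stronger readings are tempting and are not supported:

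- **The overall test costs power for nothing.** While three times remain undesignated, it is the only thing limiting error across them. At correlation 0.5 it lowers about 12.8% with no such test to 9.5% (at each time) or 3.5% (joint). It becomes redundant only once one time is fixed.
- **The error rate is 10 to 14%.** Simulated values of 10.2 to 13.8% belong to Dunnett with no overall test, which is not the procedure described.
- **All five scales are co-primary.** Read literally, the section yields 2 × 3 × 5 = 30 contrasts. The Outcome section names GARS alone as primary, so this is an inconsistency to reconcile. Unadjusted secondary scales do not inflate the GARS claim.

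**Conclusion.** The point holds for GARS across the three times. With no primary time point and no adjustment beyond Dunnett's two contrasts, strong control at two-tailed 0.05 fails under either form of the overall test. When nothing works, familywise error is about 7–10% with a test at each time or about 3–4% with one joint test. When an effect exists only at Week 5, false findings at the other two times are about 6–7% or 8–9% respectively.

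The two figures for each form belong together; taking the worse figure from each would overstate the problem. The sizes rest on assumed between-time correlations of 0.3 to 0.8 and, where an effect is placed, d = 0.6. The inflation is moderate, but it bears on what may be claimed as the trial's main result. The conflict over which scales are primary rests on the text alone.

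**What to change.** In the Statistical analysis plan section, designate GARS-j change from baseline at one pre-specified time as the primary analysis. Test book versus control and ICBT versus control there, from the mixed model, with Dunnett adjustment. Label the other times and the other four scales secondary. Week 13 is one defensible choice, being the first assessment after both recommended schedules end, but the article does not dictate it. A fixed hierarchy across the three times, or a stated adjustment over them, would also control the error.

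Once one time is fixed, the overall test can be dropped; Dunnett alone then holds 5.0% and 0 to about 2 points of power are recovered. If three times are kept, the form of any overall test must be stated, and it should not be the only protection.

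No extra participants or data are needed. The costs are that the other times and scales can no longer carry the primary claim, and that the Sample size statement of "a power (1 − *β* error probability) of 0.9 for three groups", which is for the omnibus F test, must be restated for the Dunnett contrasts. At 69 per arm and f = 0.25 that is about 81% for a single effective arm and, if both arms work equally, 92% for at least one and 70% for both. The change should be made before any data are analysed by group.

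### The stated 0.90 power belongs to a three-group omnibus F test; at least one of the two Dunnett contrasts with control that answer the trial's aim has power of about 0.81 or less

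*Protocol article*

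**What the plan says.** The Abstract states the aim as the efficacy of two self-help CBT programmes. Under Trial design these are randomised 1:1:1 with a no-treatment control.

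The Sample size section specifies a G*Power ANOVA, "fixed effects, omnibus, one‐way, with an effect size" of 0.25, with "an *α* error probability of 0.05, and a power (1 − *β* error probability) of 0.9 for three groups". It reports: "These inputs yielded a noncentrality parameter of 12.94, a critical *F* of 3.04", and "an original total sample size of 207, and an actual power of 0.902". Allowing for 20% attrition, "The sample size for this study was set at 249". It gives no pattern for the three means and no power for either programme against control.

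The Statistical analysis plan section uses mixed-effects models for change from baseline to Weeks 5, 13 and 26 and names no primary visit. It then sets the condition "If an overall significant difference is found, multiple comparisons will be conducted", and the comparison method is Dunnett's test. The overall test that opens the gate is not defined further.

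**The concern.** Rejecting equality of all three means is not the same as showing that a given programme beats control. The F test can reject because the book and ICBT arms differ from each other, or on a pattern in which neither Dunnett contrast reaches its own threshold. A reader of the Sample size section may take 0.90 as the chance of detecting an effective programme. If the chance for a given programme is nearer 0.8, the risk of missing it is about double the implied 10%, and a null result for one programme could be over-read.

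The gate raises a second question. Dunnett's test already controls the two contrasts at 5% at one time point, so requiring a significant F test first can only remove rejections there.

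**Working it through.** **Inputs.** From Sample size: f = 0.25, alpha 0.05, three groups, evaluable N = 207 (69 per arm), enrolled 249 (83 per arm), 20% attrition. From Statistical analysis plan: two-sided 0.05, Dunnett's test, omnibus condition. Assumed here: the pattern of means, and one visit without baseline adjustment.

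**1. The plan's own figure.** Noncentrality = N × f² = 207 × 0.0625 = 12.94. With 2 and 204 degrees of freedom the critical F is 3.040 and the power 0.902. This reproduces.

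**2. After attrition.** 249 × 0.8 = 199, or 66 per arm. Omnibus power at 199 is 0.890.

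**3. What f = 0.25 allows for the contrasts.** Let d1 and d2 be the standardised differences from control. With equal arms, f² = [d1² + d2² + (d1 − d2)²] / 9, so d1² + d2² + (d1 − d2)² = 9 × 0.0625 = 0.5625.
- Equal effects: 2d² = 0.5625, so d = 0.530.
- Only one programme effective: again 2d² = 0.5625, so d = 0.530.
- Graded effects (d2 = d1/2): 1.5 × d1² = 0.5625, so d1 = 0.612 and d2 = 0.306.
- Bound: if m is the smaller of |d1| and |d2|, then 2m² ≤ 0.5625 and m ≤ 0.530. The weaker contrast can never exceed d = 0.530.

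**4. Dunnett power.** Two-sided, two contrasts, pooled variance, critical |t| about 2.23; 1,000,000 simulated trials per scenario.

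| Pattern | n per arm | Ungated | Gated |
|---|---|---|---|
| Equal, each contrast | 69 | 0.81 | 0.80 |
| Equal, each contrast | 66 | 0.79 | 0.78 |
| Equal, at least one | 69 | 0.920 | 0.901 |
| Equal, at least one | 66 | 0.908 | 0.887 |
| Equal, both | 69 | 0.705 | 0.705 |
| Equal, both | 66 | 0.679 | 0.679 |
| One effective, that contrast | 69 | 0.812 | 0.803 |
| One effective, that contrast | 66 | 0.793 | 0.782 |
| Graded, stronger | 69 | 0.913 | 0.892 |
| Graded, stronger | 66 | 0.900 | 0.876 |
| Graded, weaker | 69 | 0.336 | 0.335 |
| Graded, weaker | 66 | 0.321 | 0.321 |

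Noncentral t at d = 0.530 gives 0.810 (69 per arm) and 0.791 (66 per arm), in agreement. With no attrition (83 per arm) each contrast at d = 0.530 has 0.88.

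If only one programme works, F is significant with no Dunnett rejection in 0.902 − 0.812 = 9.0% of trials at 69 per arm, and 0.888 − 0.791 = 9.7% at 66.

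**5. The gate at one visit.** Under the global null, Dunnett alone has familywise error 0.050; gated, 0.037. The cost in power is about 1 point per contrast (up to about 2.4 for the stronger one in the graded pattern) and about 2 points for at least one success.

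**6. The gate across three visits.** Global null, 66 per arm, known variance, Dunnett at each visit, assumed between-visit correlations of 0.4, 0.6 and 0.8:
- no gate: at least one false positive in 0.13, 0.12 and 0.10 of trials;
- gate on the visit-averaged group test: about 0.04 throughout;
- gate on a joint 6-df test: about 0.037, 0.033 and 0.028.

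**The case against.** The Sample size section openly labels its calculation as omnibus and never says that 0.90 applies to each programme. That is true, but it is the only power given, and it belongs to a test that does not answer the stated aim.

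A reader might infer that both contrasts are held to about 0.8 or less. The documents do not support this. No pattern of means is given, and with graded effects the stronger contrast reaches 0.90 to 0.91. What holds in every pattern is the limit on the weaker contrast. If success meant at least one programme beating control, with equal effects, gated power at 69 per arm would be about 0.90; the protocol does not define success that way.

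A reader might also infer that the gate has no benefit and can simply be deleted with familywise error kept at 5%. That holds for one visit only. The plan tests three visits and leaves the overall test undefined. If that test is joint or averaged over visits, it is the only stated protection across them. The protection is weak, since it covers the global null only, but it is not nil. The gate's cost is also small, so at one visit it is a minor inefficiency.

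Finally, 0.79 is not the power of the planned mixed model. If f is in raw-score units and baseline is adjusted for, the effective d is 0.530/√(1 − r²); assumed baseline correlations of 0.3, 0.5 and 0.6 then give 0.83, 0.90 and 0.94 per contrast at 66 per arm. If f already refers to change scores, this gain need not apply. The protocol states neither, so 0.79 must carry its assumptions.

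**Conclusion.** The point holds in a limited form. The 0.90 (0.89 after 20% attrition) is omnibus power. On the same one-visit, unadjusted basis, at least one programme-versus-control contrast has power of about 0.81 or less at 69 per arm under any pattern of means consistent with f = 0.25. This bound needs no assumption about the pattern. The specific values do: about 0.81 and 0.79 per contrast and 0.70 and 0.68 for both programmes with equal effects; 0.32 to 0.34 for the weaker programme with graded effects.

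The gap between omnibus and contrast power is the main issue. The gate is unnecessary once a single visit is tested, but it costs only 1 to 2.5 points, and removing it while three visits remain co-equal would do more harm than good.

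**What to change.** In Sample size, label 0.90 (0.89 after 20% attrition) as omnibus power only. Add that each Dunnett contrast with control has about 0.79 power at d = 0.53 with 66 per arm, and state that this is a one-visit, unadjusted calculation assuming equal effects, which baseline adjustment in the mixed model could raise.

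In Statistical analysis plan, name one primary visit for the GARS and test the two Dunnett-adjusted contrasts from the mixed model at that visit, without the omnibus condition. Treat the other visits as secondary, or adjust across them. The two changes belong together: the condition should not be dropped unless the primary visit is named or error is controlled across visits.

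This is a wording change with no extra participants. Familywise error for the two primary contrasts is then 5%. The cost is a less favourable power statement and the need to commit to one visit.
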